### Dissemination of results

During each visit, mothers will receive their infant’s growth measurements and blood haemoglobin result. The remaining blood results will be provided on request. Once available, participants who completed the intervention will receive a summary of findings in lay language, and whether they were assigned to the intervention or control. Results will be presented at national and international scientific conferences, prepared for publication in peer-reviewed journals, and circulated to the media and should be of interest to a range of audiences including families, health professionals, district health boards, academics, and primary health organisations. Individuals with substantive contributions to the design, conduct, interpretation, and reporting of the study will be recognised by granting authorship on the final relevant report.

### Data handling

Name and address details will be kept in a separate Microsoft Excel spreadsheet, and will include progress check boxes in order to track and schedule follow-ups. All entries will be cross-checked by another member of the research team. The video content to be stored on the shared storage platform OneDrive will be protected by Citrus Consulting Group Limited, a high security data management and storage company in New Zealand. Only the researcher and the participant have access to the designated video folder labelled by subject number. All data will be stored safely under confidential conditions and archived for at least 5 years, and only the researchers will have access and permissions to the final intervention dataset.

### Statistical analysis

Statistical analysis will be performed using IBM SPSS version 25.0 (IBM Corp. Released 2017, IBM SPSS Statistics for Windows Version 25.0. Armonk, NY, IBM Corp.). Data will be cleaned and checked for coding errors and completeness. To assess if data is normally distributed, the Kolmogorov-Smirnov and Shapiro-Wilk tests and normality plots will be used. Data that is not normally distributed will be transformed using log transformations to improve normality. Mean (standard deviation) and median (25, 27 percentiles) will be used to report normal and non-normal data, respectively. Transformed data will be reported at geometric mean (95% CI) following back transformation, and categorical data as frequencies.

Baseline characteristics of infants and mothers will be compared across intervention groups using the independent *t*-test or Mann-Whitney test for continuous variables (e.g. infants’ age, weight, breastfeeding duration, and mothers’ age), and chi-square tests for categorical variables (e.g. gender, milk feeding type, and mothers’ education).

For the primary analysis at 9 months, Independent t-test or Mann-Whitney test will be used to assess differences in vegetable intake and other food acceptance variables, depending on data distribution.

Additional analyses will be performed to investigate if the intake of intervention foods and mothers-rated liking and rate of acceptance after 4 weeks are correlated (using Pearson’s or Spearman’s correlations depending on data distribution).

Given the nature of the intervention, per protocol (PP) analyses will be conducted. Although this may compromise the integrity of randomisation and reduce sample size, PP should help address dilution effects of non-compliance/missing data that is associated with intention-to-treat analysis. PP may also provide more information on the efficacy of the treatment. Reasons for excluding patients (e.g. loss to follow-up, major deviations from the protocol) will be fully reported. All statistical tests will be two-tailed with an alpha value of P < 0.05, and corrections applied for multiple comparisons where indicated.

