## Methods/design

This study is designed as a randomised controlled trial comparing two parallel groups following either a “vegetables first” approach to complementary feeding or standard practice of feeding fruit and vegetables. This involves a 4-week intervention period starting from the beginning of complementary feeding (between 4 and 6 months old), with the primary endpoint of vegetable intake at 9 months of age (Fig. 1). The duration of the intervention targets the sensitive period for taste development [48], is logistically feasible, and allows for a timely progression to other foods and textures (e.g. mashed) that is expected by around 7 months. An endpoint of 9 months old aims to capture effects over time without significant loss to follow-up, and enables the study foods to be retested in an age-appropriate form before infants have transitioned to family foods at 12 months of age.

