### Participants

Mother-infant pairs (4 to 6 months old) living in Auckland will be invited to register on the study website (www.vegesfirststudy.co.nz) [49] advertised on social media, email, and community notice boards. Based on the findings of Barends and colleagues [35], we calculated that 65 participants (a minimum of 52 participants, and allowing for a 20% potential dropout rate) would be required for each arm of the trial to demonstrate a clinically significant difference at 80% power and 5% statistical significance. Power calculations used a 21-unit difference of vegetable intake (grammes) between intervention group and control, and a mean standard deviation of 43 and 29 units, respectively. The sample size was calculated using the formula below [50]:
$$ \mathrm{N}={2\upalpha}^2\mathrm{K}/{\left({\upmu}_2-{\upmu}_1\right)}^2 $$where N is the sample size required per group, SD is the pooled standard deviation, α is the SD, K is the constant (7.9 denotes 80% power and 5% significance), and (μ_2_ – μ_1_) is the difference in vegetable intake (grammes) between groups.

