### Randomisation, blinding, and concealed allocation

Eligible and consented mother-infant pairs will be randomly allocated to either the intervention or control group, having been stratified by infant gender and using a random number generator by the research trials manager who is not involved in the study design and outcome analysis. In accordance to block randomisation with a 1:1 allocation, for every block of eight participants, four will be allocated to each arm of the trial, with the block size concealed until the primary endpoint is analysed. Allocation concealment will be ensured, as the release of the randomisation code occurs only until the participant has been recruited into the trial, which is after consent and baseline measurements have been completed. After assignment, researchers will not be blinded given their necessary involvement in the food product development and subsequent familiarity with food characteristics (e.g. colour). While participants will be provided with an information sheet that lists all the types of fruit and vegetables included on the study, they will be blinded to the specific foods allocated to them as foods are labelled generically (e.g. “Green A” rather than “spinach/potato”). They will also be unaware of the RCT design, so do not know specific differences between feeding regimes. In an emergency where breaking of the study blind is needed, plans are in place for the principal investigator to reveal the treatment assignment for a given participant.

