#### Pregnancy/lactation food frequency questionnaire (FFQ) and food choices questionnaire (FCQ)

As the mother’s diet may predict infant liking and intake of vegetables, a FFQ asking about mothers’ intake of vegetables and fruit during pregnancy and lactation is adapted from an existing New Zealand validated FFQ [65]. An accompanying FCQ gains further insight on other dietary habits, such as foods avoided. These questionnaires are peer-reviewed by three experts in the nutrition and dietetics field and pilot tested with 14 new mothers. Their feedback informed minor wording changes to increase readability and acceptability, thus improving content validity; each questionnaire requires 15–20 min to complete at baseline.

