#### Baby Eating Behaviour Questionnaire (BEBQ)

As infant feeding behaviour characteristics could impact results, an online version of the validated BEBQ is to be completed [54]. This is an 18-item questionnaire with 17 items measuring four aspects of infant feeding behaviour and one item measuring general appetite before starting complementary feeding. Response options range from never = 1 to always = 5. Scoring involves calculating mean scores for each subscale with higher mean scores indicating greater presence of the feeding behaviour. The four themes are enjoyment of food (e.g. My baby seems contented while feeding), food responsiveness (e.g. My baby frequently wants more milk than I provide), slowness in eating (e.g. My baby takes more than 30 min to finish feeding), and satiety responsiveness (e.g. My baby get full up easily). This questionnaire should take 10 min to complete. It is expected that infants who enjoy food less, are less food responsive, eat slower, are less sensitive to internal cues of satiety, and have a smaller overall appetite may be more difficult to feed and perhaps less willing to accept vegetables specifically, compared to infants with the opposite traits.

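### The primary 9-month test is unadjusted: it leaves out the stratification factor and baseline variables the protocol calls possible predictors, forgoing precision of unknown size

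*Protocol article*

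**What the plan says.** The protocol article, under Statistical analysis, fixes the main comparison: "For the primary analysis at 9 months, Independent t-test or Mann-Whitney test will be used to assess differences in vegetable intake". The choice between the two tests depends on the distribution of the data. The same section allows log transformation of non-normal data and sets the error rate: "All statistical tests will be two-tailed with an alpha value of P < 0.05". Baseline characteristics have one stated use there, which is to be compared between arms by significance tests. No covariate and no adjusted model is named anywhere in the article.

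The Randomisation section says that participants are allocated "having been stratified by infant gender and using a random number generator", and that "for every block of eight participants, four will be allocated to each arm of the trial".

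Two baseline instruments are justified by their possible link to the outcome. On infant feeding behaviour: "As infant feeding behaviour characteristics could impact results, an online version of the validated BEBQ is to be completed". On the mother, her "diet may predict infant liking and intake of vegetables". Under Data collection, both are to be completed before the first visit, so before allocation is released.

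Under Methods/design, the 4-week intervention runs "starting from the beginning of complementary feeding (between 4 and 6 months old"), and the endpoint is at 9 months of age.

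**The concern.** Stratified randomisation takes the between-sex difference out of the true variance of the treatment estimate. A test that ignores the stratum puts that variance back into the estimated standard error. If sex is related to intake, the interval is then wider than the design warrants.

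The same argument, without the design obligation, applies to the BEBQ and maternal diet. The protocol gives reasons for expecting them to matter, collects them before allocation, and does not use them to sharpen the comparison. Testing baseline differences between arms does not improve the estimate.

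Age is a further candidate. Solids begin between 4 and 6 months and the intervention lasts 28 days, so it ends at about 5 to 7 months. The test is at 9 months, which leaves a gap of roughly 2 to 4 months. The planned test makes no allowance for this spread.

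At stake is precision in a trial with about 50 evaluable infants per arm.

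**Working it through.** **Inputs.** From Participants in the protocol article: difference 21 g, SDs 43 and 29 g, 52 evaluable per arm, 65 recruited per arm, 20% dropout. The constant is also given there: "K is the constant (7.9 denotes 80% power and 5% significance"). The test is two-sided at 5% (Statistical analysis). The abstract gives 120 pairs in total. The share of outcome variance explained by covariates (R²) is not given, so it is an **assumption**, shown from 0 to 0.30.

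**The plan's own figure.** Pooled SD = √((43² + 29²)/2) = 36.67 g. The stated formula gives N = 2 × 36.67² × 7.9 / 21² = 48.2, so 49 per arm. Using the arithmetic mean SD of 36 gives 46.4, so 47. The stated 52 does not follow from the formula but errs on the safe side. The dropout step does follow: 52 / 0.80 = 65. No covariate adjustment is assumed in the sample size.

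**Gain from a set of baseline covariates.** The residual SD becomes 36.67 × √(1 − R²). Power comes from the noncentral t distribution with noncentrality 21 / (residual SD × √(2/n)). The 95% half-width is t × residual SD × √(2/n); unadjusted with 52 per arm it is 1.983 × 36.67 × √(2/52) = 14.3 g. The second sample size is the abstract's 120 pairs less 20%: 60 × 0.80 = 48 per arm.

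| Assumed R² | Residual SD (g) | Power, 52 per arm | 95% half-width, 52 per arm (g) | Power, 48 per arm |
|---|---|---|---|---|
| 0 (unadjusted) | 36.67 | 82.4% | 14.3 | 79.3% |
| 0.02 | 36.31 | 83.2% | 14.1 | 80.1% |
| 0.05 | 35.75 | 84.3% | 13.9 | 81.3% |
| 0.10 | 34.79 | 86.2% | 13.5 | 83.3% |
| 0.20 | 32.80 | 89.9% | 12.8 | 87.4% |
| 0.30 | 30.68 | 93.3% | 11.9 | 91.3% |

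Taking off four degrees of freedom for four covariates changes these powers by at most 0.1 point.

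**Sex alone.** This was simulated with 20,000 replicates per setting, 52 per arm, equal numbers of each sex, allocation balanced within sex, and total SD held at 36.67 g.

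| Variance explained by sex (assumed) | Type I error, unadjusted | Power, unadjusted | Power, sex-adjusted |
|---|---|---|---|
| 0% | 4.9% | 82.4% | 82.4% |
| 2% | 4.8% | 82.3% | 82.8% |
| 5% | 4.6% | 83.1% | 84.4% |
| 10% | 3.9% | 83.6% | 86.0% |
| 20% | 3.0% | 84.8% | 89.6% |

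The sex-adjusted test kept its type I error between 4.9% and 5.3% throughout; the simulation error near 5% is √(0.05 × 0.95 / 20,000) = 0.15 points. Leaving out the stratum therefore makes the test conservative, never liberal. The loss is negligible unless sex explains about 5% of the variance or more.

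**Which variables precede allocation.** Infants must not have started solids at entry (Inclusion and exclusion criteria). The allocation is released only after consent and baseline measurements (Randomisation). The study foods are the first foods (abstract). Age at first food is therefore set after allocation, whereas sex, age at randomisation, the BEBQ and the maternal questionnaire are known before it.

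**The case against.** The strongest reply is that nothing here is invalid. Under randomisation the unadjusted difference is unbiased, and its standard error already allows for chance imbalance. The sample size was set for an unadjusted comparison, and 52 per arm exceeds the 80% target. This stands, so the point concerns efficiency only.

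A second reply is that the predictors may be weak. A reader might infer from the protocol's rationale that strong predictors are being discarded. The documents do not support that: the wording is tentative, no correlation is given, and no baseline value of the outcome can exist in infants who have eaten no solids. This also stands. At R² of 0.02 to 0.05 the gain is only 1 to 2 points.

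A third reply is that the article is condensed and an adjusted analysis may sit in a fuller plan. This stands only in part. Secondary or sensitivity models could well be there, but the article does not leave the primary method open: it names two tests, neither of which takes a covariate.

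A fourth reply is that a regression on raw grams would lose the plan's provision for skewed data. This is correct, and the remedy has to keep that provision.

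**Conclusion.** The point holds as a matter of efficiency. The primary test omits the one factor on which randomisation is stratified, and baseline variables that the protocol itself regards as possible predictors. The cost is some unneeded conservatism if sex is prognostic, and a loss of power between 0 and about 11 points at 52 per arm over an assumed R² of 0 to 0.30. The true value cannot be read from the document.

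Two stronger readings should be resisted. One is that the omission leaves the trial underpowered: at the stated 52 per arm it does not, since unadjusted power is about 82%. With the abstract's 120 pairs and 20% dropout it is 79.3%, but that small shortfall comes from the smaller number of infants. The other is that the omission biases the estimate or inflates the type I error. It does neither; the simulated error was at or below 5%.

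The figures rest on the protocol's 21 g and SDs of 43 and 29 g, roughly normal outcomes, and a linear relation between covariates and intake.

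**What to change.** Prespecify as the primary analysis a linear model of 9-month test-meal vegetable intake on arm, infant sex, age at randomisation, baseline BEBQ score (naming the subscale or item) and maternal vegetable intake from the baseline questionnaire. Use age at randomisation, not age at first food, which is set after allocation. Keep the existing allowance for log transformation when intake is skewed, and say how a zero intake would be handled on that scale. Report the adjusted difference with its 95% CI, or the ratio of geometric means if logs are used. Keep the t-test or Mann-Whitney comparison as supportive.

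The cost is a sentence or two in the Statistical analysis section, written before outcome data by arm are seen. Every covariate is already collected before allocation, and the sample size need not change.

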### Inclusion and exclusion criteria

Infants will be eligible for this study if they are born term (37 weeks or greater), of normal growth/weight, and have no known food allergies, chronic diseases, or medical conditions. Infants must not have started complementary feeding and must live in Auckland. Mother’s proficiency in English is needed given the requirement to complete assessment tools as part of the secondary outcomes. Participants will be excluded if they demonstrate repeated non-adherence to key study procedures or are not able to complete the 4-week intervention period.

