### Data collection

Mothers will be emailed the links to the online demographics, baby behaviour, and pregnancy/lactation food frequency questionnaires to complete at home before their first visit to the HNRU at which other baseline data (infant anthropometry and blood samples) will be collected. The 4-week intervention and primary data collection (mother reported infant vegetable liking and intake, video-recorded meals) will take place in the infant’s home environment from May 2019 to October 2021. Follow-up data (anthropometry and/or blood samples) will be collected at 9, 12, and 24 months of age at the HNRU; home visits will be available as required. In the instance where visits are not possible, mothers will be asked to provide current infant growth measurements (following standardised instructions given by the researcher) and food diaries by email or post. Virtual meetings using Zoom or Skype will be available for additional support. Additional child vegetable/fruit liking and food frequency questionnaires will be completed by mothers at home when their infant is 9, 12, and 24 months old. To the extent possible, we will continue to collect data for all outcome measures for participants who discontinue or deviate from the intervention protocols, while anticipating and planning for missing data. Given the potential for this cohort to provide valuable data for future early life nutrition research, additional outcome measures will be collected. These include mothers’ iron status/vitamin D status (at baseline), infants’ vitamin D status (at baseline), and infant stool samples for microbiota analysis (pre- and post-4-week intervention, and all follow-ups). Such data may be useful to assess maternal iron status 6 months post-partum or infant vitamin D status and links to the microbiome. Table 2 outlines the primary study outcome measures and testing methods. Figure 3 provides the schedule of enrolment, intervention, and assessment.

**Table 2 Tab2:** Summary of the study outcome measures and methods

Variables	Method
Primary outcomes	
Vegetable liking	Liking tool (Appendix A). Completed by mother at home
	Rate of acceptance video coding tool. Mother video-records meals. Independent researcher codes infant behaviours
	Child vegetable and fruit liking questionnaires. Completed online by mother
Vegetable intake	Weighed food diary. Completed by mothers at home
	FFQ. Completed online by mother
Blood analysis^a^	

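### Per-protocol is the only analysis set named, adherence is a post-randomisation exclusion, and no as-randomised comparison is planned

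*Protocol article*

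**What the plan says.** All references are to the protocol article.

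- **Statistical analysis** fixes the analysis set: "Given the nature of the intervention, per protocol (PP) analyses will be conducted". The reason follows: "Although this may compromise the integrity of randomisation and reduce sample size, PP should help address dilution effects of non-compliance/missing data". The sentence attributes this dilution to intention-to-treat, which the article mentions nowhere else. The section then promises: "Reasons for excluding patients (e.g. loss to follow-up, major deviations from the protocol) will be fully reported".
- **Inclusion and exclusion criteria** ends with: "Participants will be excluded if they demonstrate repeated non-adherence to key study procedures or are not able to complete the 4-week intervention period".
- **Randomisation, blinding, and concealed allocation** times release of the code, "which is after consent and baseline measurements have been completed". The four-week feeding period comes later, so the adherence and completion exclusions fall after randomisation.
- **Data collection** says, qualified by what is possible: "we will continue to collect data for all outcome measures for participants who discontinue or deviate from the intervention protocols".
- **Background** and **Discussion** present the trial as randomised evidence of cause and effect that may inform feeding recommendations.

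**The concern.** Randomisation makes the arms comparable at allocation. A set defined by what happens afterwards keeps that comparability only if the reasons for leaving it are unrelated to arm or unrelated to outcome. Here neither can be assumed in advance. Under Infant foods, Table 1 gives the intervention arm spinach with potato, potato, beetroot with potato, and green bean. The control arm gets mainly apple and pear, plus pumpkin. The Background says that infants may find bitter taste hard to accept. A family whose infant struggles with the vegetable purées could give up or substitute other foods more often than a family in the control arm.

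The primary outcome is vegetable intake at 9 months. Losing poor vegetable acceptors mainly from the intervention arm would raise that arm's mean with no true effect. No planned analysis would show whether this had happened, because none compares the arms as randomised. The practical question, what happens when families are asked to start with vegetables, also includes infants who do not take to them.

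**Working it through.** **Inputs.** From Participants: difference 21 g, SDs 43 and 29, 52 evaluable and 65 recruited per arm, two-sided 5%. Pooled SD = √((43² + 29²)/2) = √1345 = 36.67 g. Assumed, because the documents give no values: the fraction excluded in each arm, and the correlation r between early acceptance and 9-month intake.

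**The plan's own figure.** The printed formula gives 2 × 1345 × 7.9 / 21² = 48.2, so 49 per arm, not 52. The dropout step reproduces: 52/0.80 = 65. The gap between 49 and 52 is a separate matter and does not affect this point.

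**Bias under no true effect.** If the least-accepting fraction f of an arm is removed, the mean of those who remain rises by SD × r × λ(f), where λ(f) = φ(z_f)/(1 − f), z_f is the normal quantile of f and φ is the normal density. The spurious difference is SD × r × [λ(f_I) − λ(f_C)].

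- λ(0.20) = 0.2800/0.80 = 0.350; λ(0.05) = 0.1031/0.95 = 0.1086.
- 20% versus 5%, r = 0.5: 36.67 × 0.5 × (0.350 − 0.1086) = 4.4 g. Simulating whole infants (13 and 3 of 65 removed, pooled t-test) gives 4.5 g.
- Type I error, same scenario: the variance in each arm shrinks by 1 − r²λ(λ − z_f), that is 0.896 and 0.952. SE = 36.67 × √(0.896/52 + 0.952/61.75) = 6.63 g. Shift = 4.43/6.63 = 0.67 SE. Rejection probability = Φ(0.67 − 1.96) + Φ(−0.67 − 1.96) = about 10%; simulation gives 11%.
- Half the exclusions random: only 10% and 2.5% are acceptance-driven. λ(0.10) = 0.195 and λ(0.025) = 0.0599, so 36.67 × 0.5 × 0.135 = 2.5 g. Simulated with whole infants (6 of 13 and 2 of 3 acceptance-driven) it is 2.0 g. The gap is rounding to whole infants.

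| Excluded, intervention vs control | r | Acceptance-driven | Spurious difference | Type I error |
|---|---|---|---|---|
| 20% vs 0% | 0.5 | all | 6.4 g | 16% |
| 20% vs 5% | 0.5 | all | 4.5 g | 11% |
| 20% vs 5% | 0.5 | half | 2.0 to 2.5 g | 6 to 7% |
| 15% vs 5% | 0.3 | all | 1.8 to 1.9 g | about 6% |
| 20% vs 20% | 0.5 | all | 0 | close to 5% |

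Against the planned 21 g, 4.5 g is 21% and 2.0 g is about 10%.

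**Cost of analysing as randomised.** Let a fraction f of the intervention arm be wholly non-adherent and get no effect. The expected difference is 21(1 − f), and power = Φ(21(1 − f)/(SD√(2/n)) − 1.96). For n = 65 the SE is 36.67 × √(2/65) = 6.43 g. At f = 10%, 18.9/6.43 − 1.96 = 0.98, so power is 0.836.

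| Observed per arm | f = 0 | f = 10% | f = 20% |
|---|---|---|---|
| 65 | 0.904 | 0.836 | 0.743 |
| 60 (the abstract's 120 pairs) | 0.880 | 0.806 | 0.709 |
| 52 | 0.831 | 0.748 | 0.646 |

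**The case against.** **The choice is open and reasoned.** The authors concede the cost to randomisation, say that per-protocol may tell more about efficacy, and promise to report reasons for exclusion. That is transparent, but it does not remove the selection. Nor can this be left to an unseen analysis plan, because the article itself names the set and argues for it. The word only does not appear, but no other set does either.

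**Refusal is not non-adherence.** A reader might infer that infants who reject vegetables will be excluded. The documents do not say so. Under Compliance to study protocol, the weekly questionnaire asks on how many days the food was offered and what else was consumed. Under Liking tool, three consecutive refusals simply end the meal. An infant who refuses every spoon can be fully adherent. The barrier named in the Discussion is families' difficulty with procedures, which need not differ by arm, and mothers do not know their specific foods or the trial design. This stands: imbalance is possible but not shown.

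**The scenarios are assumptions.** Driving every exclusion by acceptance is close to the worst case, and the milder rows show little inflation. This stands too.

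**Two further readings go too far.** One is that deviators' data will certainly exist and be thrown away: collection is promised only as far as possible, and nothing says that the data are discarded. The other is that per-protocol is said to solve missing data: the sentence concerns dilution arising from non-compliance and missing data. The reason is still weak, since leaving infants out conditions on completion.

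**Dilution is a real cost.** At 20% complete non-adherence, power with 65 per arm falls to 0.743, against 0.831 for 52 per arm at the full 21 g. That is a reason to keep a per-protocol analysis, not to make it the only one.

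**Conclusion.** The point holds in this form: the article names per-protocol as its sole analysis set, makes adherence and completion exclusions after randomisation, and plans no as-randomised comparison, while presenting the trial as evidence of cause and effect. That gap is on the page and does not depend on any assumed rate.

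The size of any bias does depend on assumptions. It favours the hypothesis only if exclusion is both related to acceptance and heavier in the intervention arm. With 20% versus 5% excluded and r = 0.5 it is about 4.5 g with 11% type I error if acceptance drives all exclusions, about 2.0 to 2.5 g with 6 to 7% if half are random, and nil if exclusion is equal. The documents do not support saying that the result will be biased, only that the plan has no protection if these conditions arise.

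**What to change.** In Statistical analysis, make the primary 9-month comparison as-randomised: all randomised infants in their allocated arm, whatever their adherence, using every available 9-month outcome. This still leaves out infants with no 9-month record. So add a sensitivity analysis with multiple imputation from baseline and week-1 and week-4 data, imputed within arm because the foods differ. Keep per-protocol as a labelled secondary analysis.

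In Inclusion and exclusion criteria, remove the adherence and completion sentence from eligibility and use it only to define the per-protocol set. That also brings it into line with the commitment under Data collection to follow deviators.

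The cost is wording in two sections and a little extra analysis, with no new data collection. The price in power should be stated openly: for 21 g with 65 per arm observed, about 0.84 at 10% and 0.74 at 20% complete non-adherence in the intervention arm, and lower if fewer infants are observed (0.75 and 0.65 with 52).
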